**3.6.4 Treatment compliance**

For each subject, the dosage and administration time of each drug used in each course of treatment should be recorded in the CRF table. The reasons for delayed administration, drug reduction or missed administration should also be recorded in CRF.

Subjects' compliance with the treatment and protocol included voluntary compliance with all aspects of the protocol, including all blood collection required to comply with the safety assessment. If the subjects do not complete the follow-up or take medicine on time, they can be excluded from the study according to the opinions of the main researcher or the sponsor.

**3.7 Study Endpoint**

To assess the safety and activity of Anlotinib plus Sintilimab among treatment-naïve mCRC patients. Study endpoint included ORR, DCR, PFS, OS, safety.

**3.7.1 Efficacy Evaluation**

The antitumor effect will be evaluated in accordance with RECIST version 1.1 every 6 weeks.

The primary study endpoints for the study were objective response rate (ORR, complete or partial response according to RECIST version 1.1).

Secondary study endpoints included disease control rate (DCR, the proportion of patients who achieved a complete response, a partial response, or stable disease), progression-free survival (PFS), overall survival (OS) as well as safety.

PFS was defined as the time from therapy initiation to progression according to RECIST.

OS is defined as the time from therapy initiation to death from any cause.

Depth of response (DPR) was defined the percentage of maximum tumor reduction achieved in treatment compared with baseline. In case of CR, DPR is 100%.

Remission maintenance time was calculated in all PR or CR patients who were confirmed to meet RECIST 1.1 criteria. The duration of remission is the time from the first record to PR or Cr until death or disease progression (based on the first occurrence). As of the date of analysis, the deadline was the date of their last imaging evaluation.

**3.7.2 Safety**

All patients who have received at least one study medication will be regarded as the effective population for safety analysis. The physical examination results, vital signs, adverse events and laboratory abnormal values of patients will be summarized. All adverse events should be reported and graded according to NCI common adverse event Terminology Standard (CTCAE) version 5.0.

**3.7.3 Starting Time of study**

The time of starting the study was defined as the date of signing the informed consent.

**3.7.4.1 Treatment period**

- The screening phase should be conducted within 28 days before the start of study drug treatment.
- Treatment period refers to the interval from the use of the first drug treatment to the withdrawal of the patient from the study drug treatment.
- Patients will enter the post-treatment follow-up period after discontinuing the study drug treatment. This period should include contacting the patient every 3 months until 1 year after progression or recording the patient's death to collect the data of overall survival.

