Secondary study endpoints: Disease Control Rate (DCR, the proportion of patients who achieved a complete response, a partial response, or stable disease), Progression-Free survival (PFS), overall survival (OS) as well as safety. PFS was defined as the time from therapy initiation to progression according to RECIST. OS is defined as the time from therapy initiation to death from any cause.

Exploration study endpoints: biomarker analysis including PD-L1 expression, TMB, molecular alteration profile, tumor immune-microenvironment, plasma exosome miRNA.

1. **Method**
   1. **Study design**

APICAL-CRC trial was an investigator-initiated, open-label, non-randomized, single-arm, phase II clinical trial using Simon’s minimax two-stage design. The combination of anlotinib plus sintilimab is expected to result in an improved ORR of 35%. The null hypothesis, which stated that the true ORR was 15%, would be tested against a one-sided alternative of 35%, with 80% power and a type I error rate of 5%. In the first stage, the study accrued 15 patients. If less than two response or no response was observed, the study was terminated and deemed negative. Otherwise, an additional 13 patients would be accrued for the second stage. The study was considered positive if there were more than 9 responders among the 28 patients.

- 1. **Single-arm**

This trial design is a single-arm study without control group.

- 1. **Participants**

According to the inclusion criteria, all patients required to be treatment-naïve advanced CRCs

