**3.8.5** **Follow up after disease progression**

Get in touch with the patients every 3 months (visit or telephone) to get the information about the overall survival and chemotherapy after the study. Follow up should be carried out every 3 months until one year after the patient progressed or died. The following information should be obtained during each follow-up:

• The survival status of the patients.

• Disease status and progression date (if applicable).

• Date of death (if applicable).

• All new anticancer treatments were recorded.

Note: CRCs Patients with prognosis disease should be treated like other patients with advanced colorectal cancer.

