**5.1.3.2** **Secondary study endpoints**

Secondary study endpoints included disease control rate (DCR, the proportion of patients who achieved a complete response, a partial response, or stable disease), progression-free survival (PFS), overall survival (OS) as well as safety.

PFS was defined as the time from therapy initiation to progression according to RECIST.

OS is defined as the time from therapy initiation to death from any cause.

Depth of response (DPR) was defined the percentage of maximum tumor reduction achieved in treatment compared with baseline. In case of CR, DPR is 100%.

Remission maintenance time was calculated in all PR or CR patients who were confirmed to meet RECIST 1.1 criteria. The duration of remission is the time from the first record to PR or Cr until death or disease progression (based on the first occurrence). As of the date of analysis, the deadline was the date of their last imaging evaluation.。

Kaplan Meier method was used to get the expected survival curve of the patients including PFS and OS.

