**7.5 Flow-chart of study**

|  | Before-treatment | 21days for one cycle | | | | At the end of study | At the end of study to PD | After PD_10_ |
| --- | --- | --- | --- | --- | --- | --- | --- | --- |
|  |  | 1^st^ cycle | 2^nd^  cycle | 3^rd^  Cycle | 4^th^  to PD or treatment terminated |  |  |  |
| Items | Screening | Day1 | Day1 | Day1 | Day1 | Within 7 days | Every 8 weeks | Every 3 months |
| Informed consent of patients | X（within 28 days） |  |  |  |  |  |  | The following information was collected by telephone or outpatient visit every 2 months  1. Survival information of patients;  2. Changes in the treatment of cancer, including all new treatments |
| Medical History _1_ | X（within 7 days） |  |  |  |  |  |  |  |
| Complete physical examination_2_ | X（within 7 days） |  |  |  |  |  |  |  |
| Inclusion/exclusion Criteria | X |  |  |  |  |  |  |  |
| Random | X |  |  |  |  |  |  |  |
| Vital signs and ECOG |  | X | X | X | X | X | X |  |
| ECG | X（within 28 days） |  | X | X | X | X |  |  |
| CT and MRI _3_ | X（within 28 days） |  | | | |  |  |  |
| Imaging Evaluation_4_ | X（within 28 days） | X （每6周)-- -------------🡪 | | | | | |  |
| Hematological Examination_5_ | X（within 7 days） |  | X | X | X | X |  |  |
| Biochemical examination_6_ | X（within 7 days） |  | X | X | X | X |  |  |
| Urine test_7_ | X（within 7 days） |  | X | X | X | X |  |  |
| Serum pregnancy test | X（within 7 days） |  | | | | |  |  |
| QLQ_8_ |  | X_9_ |  |  | Before 5^th^ cycle or 9^th^ cycles | X |  |  |
| Use Drug |  | X | X | X | X | X |  |  |
| AE evaluation | -- -------------🡪 | | | | | | |  |
| Concomitant disease and drug combination | -- -------------🡪 | | | | | | |  |

1. Complete medical history, demographic data, previous surgery history, concomitant diseases, allergic history, and smoking history.
2. Complete physical examination, ECOG score, NYHA heart disease classification, height, weight, vital signs and detailed examination of the body system
3. Only patients with neurological symptoms at baseline required head CT / MRI to exclude brain metastases
4. During chemotherapy, tumor assessment is performed every 8 weeks. After treatment, CT scan was required every 8 weeks until the disease progressed. If the patient withdraws from the study due to disease progression, a review of CT scan is not required at the end of the study。

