5. Hematological test: hemoglobin, hematocrit, platelet, leukocyte, neutrophil absolute value, lymphocyte absolute value, which can be checked one day before each course of treatment。
6. Biochemical tests: blood glucose, calcium, phosphorus, sodium, potassium, chlorine, creatinine, blood urea nitrogen, total protein, albumin, alanine aminotransferase, aspartate aminotransferase, alkaline phosphatase, total bilirubin, etc., which can be checked one day before each course of treatment.
7. Urine tests: urine specific gravity, PH value, urine sugar, urine protein and occult blood. In the screening period, urine test is required in the laboratory, and urine test paper can be used in the subsequent course of treatment.
8. Patients should be followed up every 3 months until 1 year or death.

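### Survival contact ends 1 year after each patient's own progression, so OS censoring depends on progression; Kaplan-Meier OS beyond about 13 months is probably overstated and deaths go uncollected

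*Protocol*

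**What the plan says.** - **Endpoint.** Sections 3.7.1 and 5.1.3.2: "OS is defined as the time from therapy initiation to death from any cause".
- **Analysis.** Section 5.1.3.2: "Kaplan Meier method was used to get the expected survival curve of the patients including PFS and OS". The synopsis (Statistical matters) adds a median with 95% CI.
- **End of survival contact.** Section 3.7.4.1: "contacting the patient every 3 months until 1 year after progression or recording the" patient's death, with OS data as the stated purpose. Section 3.8.5: "Follow up should be carried out every 3 months until one year after the patient progressed or died". These two agree.
- **Flow chart (7.5).** The After PD column is headed every 3 months, but its cell reads "The following information was collected by telephone or outpatient visit every 2 months" and gives no end. Note 8 reads "Patients should be followed up every 3 months until 1 year or death", without saying what the year is counted from.

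No section carries survival contact on to a common cut-off date.

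**The concern.** Kaplan-Meier assumes that patients censored at a given time have the same future risk as those still under observation. Here a survivor is censored at own progression time plus 12 months. From about month 13, the risk set contains only patients who are progression-free or progressed within the past 12 months. Those who progressed longer ago are still at risk of death but have been removed.

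The design has no control arm, so OS will be read against outside data and nothing inside the trial offsets a distortion. An analysis plan cannot repair this later, because the deaths after the stop are never collected.

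**Working it through.** **No figure to reproduce.** The protocol states no expected OS, number of deaths or OS precision, so the check is a simulation on stated assumptions.

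**Inputs from the protocol**
- 28 patients (3.1) and about 1 per month, total study about 2-3 years (Study Time). At 1 per month, 28 patients take 28 months, although that section says about 20; 28 months is used here.
- Scans every 6 weeks (3.7.4.2).
- Median PFS of 6.3 months, the introduction's figure for the cited later-line study of regorafenib plus nivolumab. Its use here is an assumption.

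**Further assumptions.** Median PFS of 10 months as an alternative; median post-progression survival (PPS) of 6, 12 or 18 months; death only after progression.

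**Step 1: where the rule starts to act.** Six weeks is 42/30.44 = 1.4 months, and 1.4 + 12 = 13.4 months. Up to about 13 months the rule censors nobody, so the curve there, and any median below that point, is untouched. In the simulations the true and Kaplan-Meier curves coincide at 12 months.

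**Step 2: what sets the direction.** Model: OS = P + Q, where P is time to progression and Q is PPS; censoring at P + 12. After month 13, Kaplan-Meier replaces the death hazard of everyone alive by that of patients who are progression-free or within 12 months of progression. If the removed patients have the higher hazard, OS is overstated; if the hazard falls enough with time since progression, the sign reverses.

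**Step 3: large-sample size** (400,000 patients per scenario, progression on the 6-week grid).

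| PPS hazard | Median PFS / PPS (months) | Median OS, true vs KM | 24-month OS, true vs KM |
|---|---|---|---|
| Constant | 6.3 / 6 | 15.6 vs 15.7 | 26.1% vs 29.1% |
| Constant | 6.3 / 12 | 22.4 vs 23.8 | 46.2% vs 49.5% |
| Constant | 10 / 12 | 27.3 vs 31.0 | 56.8% vs 60.6% |
| Constant | 10 / 18 | 34.1 vs 41.5 | 67.0% vs 70.3% |
| Rising (Weibull shape 1.5) | 6.3 / 12 | 21.4 vs 24.1 | 41.9% vs 50.2% |
| Falling (shape 0.6) | 6.3 / 12 | 23.9 vs 23.6 | 49.8% vs 49.2% |
| Falling (shape 0.4) | 6.3 / 12 | 25.2 vs 23.5 | 51.3% vs 49.0% |

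- With constant hazard, 24-month OS is overstated by 3.0 to 3.8 points in these rows.
- With constant or rising hazard, or frailty shared by PFS and PPS, the bias was upward in all 15 scenarios run, by about 3 to 8 points at 24 months.
- With frailty in PPS only, it was close to nil at PFS 6.3 / PPS 12 (28.9 vs 29.1 months) and upward at 10 / 12 (35.4 vs 37.9).

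**Step 4: inside the protocol's time frame** (28 patients, 1 per month, cut-off at 36 months, constant hazard, 6.3 / 12).
- Progression in continuous time: 13.9 deaths with full follow-up, 10.7 under the rule, a loss of 3.2. Median not reached in 6% vs 31% of trials.
- Progression on the scan grid, entry one month later: 12.8 vs 10.1 deaths; median not reached in 9% vs 34%.

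**Step 5: the follow-up texts side by side.** Sections 3.7.4.1 and 3.8.5 and the After PD column header say every 3 months; the cell beneath that header says 2. Only note 8 leaves the origin of the year open.

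**The case against.** **A reader might infer that the OS median is certainly biased upward.** The documents do not support that. Upward is likely, since patients who progressed long ago usually fare worse than those still progression-free. But the protocol gives no PFS or PPS, and the sign changes under a falling hazard.

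**A reader might infer a very large effect.** With unlimited follow-up and constant hazard, the rule censors 25% to 63% of patients for median PPS of 6 to 18 months. Within the protocol's 2-3 years, it is the first cause of censoring in about 25-29%, because the cut-off itself censors many others. Medians near 40 months could not be observed in that time. A shift of 3 to 4 points at 24 months is also small against sampling error: even with all 28 patients followed to 24 months, the standard error at 46.2% is √(0.462 × 0.538 / 28) = 9.4 points. This objection stands as to size. The loss of deaths and of an estimable median remains.

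**A reader might infer three competing follow-up rules.** Note 8 more plausibly belongs to the After PD column: that header carries marker 10 while the notes stop at 8, and marker 8 sits on the quality-of-life row, which the text does not fit. Read that way, it agrees with the body. What remains is the 2 versus 3 months and the unstated origin. The interval matters little for OS, since section 3.8.5 records the date of death.

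**OS is secondary.** True; the ORR decision does not depend on it.

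**Conclusion.** The point holds in limited form. That OS censoring depends on progression follows from sections 3.7.4.1 and 3.8.5 alone and needs no assumption. Kaplan-Meier OS beyond about 13 months is probably overstated: by about 3 to 4 points at 24 months under constant hazard, and near zero or downward if the hazard falls after progression. The more dependable cost is lost information, roughly 3 of 13 to 14 deaths and a median not reached in about a third of trials instead of under a tenth. Those figures rest on assumed medians of 6.3 and 12 months and a 36-month cut-off. The flow-chart conflict on the interval is real but minor. The matter should be corrected; it does not threaten the primary conclusion.

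**What to change.** Put one rule in sections 3.7.4.1 and 3.8.5, the After PD column and note 8 of the flow chart. Contact every treated patient for survival at one stated interval until death, withdrawal of consent to follow-up, or one common data cut-off, regardless of the date of progression. Censor survivors at the date last known alive. Correct the flow-chart footnote numbering at the same time.

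If the 1-year stop has to stay, report OS only up to 12 months from first dose, where the rule can censor nobody, and give no median beyond that.

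The cost is a wording change in four places and some extra telephone contacts for at most 28 patients. The fallback costs only the later part of the curve and any later median. Neither changes treatment or the ORR analysis.

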**3.7.4.2 Imaging Evaluation**

- Screening Phase: CT or MRI scans of the chest and abdomen must be performed within 28 days before enrollment, and the measurement of the tumor should be recorded in CRF according to RECIST 1.1
- Treatment Phase：CT or MRI scan should be performed at least every 6 weeks + / - 5 days to evaluate the lesions, and the measurement of tumor should be recorded in CRF according to RECIST 1.1. Other examinations were performed according to the symptoms.
- At the end of the study：CT or MRI scan was used to evaluate the lesion, and the measurement of tumor was recorded in CRF according to RECIST 1.1. Other examinations were performed according to the symptoms。

**3.8** **Trial Phase**

**3.8.1 Screening Phase**

Within 28 days before the start of study drug use

- - - Sign the informed consent before any operation related to the study;
    - The 12-lead electrocardiogram (ECG) in the baseline period was examined and signed by the researcher;
    - Only when there are neurological symptoms (suggesting brain metastasis), brain CT scan or brain MRI should be used to exclude brain metastasis;
    - Baseline tumor assessment: at least CT and MRI scans of the target lesions can be performed within 28 days before the start of study drug use

Screening period - within 7 days before the start of study drug treatment

- - - The stage and grade of the tumor at the time of diagnosis were recorded/confirmed;
    - Demographic information, medical history, surgical history, including previous anti-cancer treatment.
    - Complete physical examination (PE), including ECOG score, height, weight and detailed systematic examination.
    - Vital signs (including heart rate, blood pressure, respiratory frequency and body temperature).
    - All concomitant diseases, concomitant drugs and their indications were recorded
    - Blood routine examination: hemoglobin, platelet count, white blood cell count and classification, including the absolute number of neutrophils and lymphocytes.
    - Complete blood biochemical examination: including blood glucose, calcium, phosphorus, sodium, potassium, chlorine, creatinine, blood urea nitrogen (BUN), total protein, albumin, alanine aminotransferase (ALT), aspartate aminotransferase (AST), alkaline phosphatase, total bilirubin, etc.
    - Urine pregnancy test was performed on all women of childbearing age. Women who have been postmenopausal for at least one year and who have undergone sterilization are not required to undergo pregnancy tests.
    - Urine routine examination: including urine white blood cells, urine red blood cells, urine sugar, urine protein and occult blood

**3.8.2 Treatment Phase**

The treatment period was 21 days. The efficacy was evaluated every 2 courses. The laboratory examination, imaging assessment and AE assessment in the treatment stage are shown in the flow chart.。

**3.8.3** **At the end of the study**

At the end of study (not due to progression), the patients should be examined every 3 months until the disease progresses (see the flow chart).

**3.8.4 Temporary visit**

Temporary visit should be conducted according to clinical needs. The corresponding clinical laboratory abnormalities and adverse events should be recorded in CRF and original data. If multiple laboratory tests are performed on the same day, only one set of test values needs to be recorded in CRF. However, all abnormal values in repeated laboratory tests should be recorded in CRF.

**3.8.5** **Follow up after disease progression**

Get in touch with the patients every 3 months (visit or telephone) to get the information about the overall survival and chemotherapy after the study. Follow up should be carried out every 3 months until one year after the patient progressed or died. The following information should be obtained during each follow-up:

• The survival status of the patients.

• Disease status and progression date (if applicable).

• Date of death (if applicable).

• All new anticancer treatments were recorded.

Note: CRCs Patients with prognosis disease should be treated like other patients with advanced colorectal cancer.

**3.9 Data quality**

In order to follow the guidelines of clinical practice (GCP), investigator will take responsibility of ensure compliance with the study protocol, GCP and relevant laws including on-site inspection of the completeness and clarity of the case report form (CRF), cross checking with the original documents, and clarification of management matters.。

**3.10 Data File**

The data in the case report form (CRF) must be consistent with the original documents, or be directly recorded in the CRF. In the case of being directly recorded in the CRF, the recorded content will be regarded as the original data. The parameters of the original data must be verified, and the information of the data source must be recorded. The research documents and all the original materials should be kept.

1. **Ethical and legal issues**

**4.1 Ethics Committee (EC) or institutional review board (IRB)**

According to the requirements of GCP, Chinese laws and regulations and relevant organizations, the study should obtain approval documents from the corresponding ethics committee/institutional review committee before the start of the research. If necessary, the extension, amendment or review of the ethics committee's approval must be obtained and handed over to the researcher. The study protocol and all amendments were approved by the Research Ethics Board of Shanghai Changzheng Hospital and was done in accordance with the Declaration of Helsinki. All patients were required to provide written informed consent.

**4.2 The ethical guidance of this study**

The procedures for operation, evaluation and documentation involved in this study protocol are to ensure that researchers follow the guidelines of clinical practice and the guidelines detailed in the Helsinki declaration. The implementation of this study will also follow the corresponding laws and regulations in China.

The investigators were not allowed to modify the study protocol without consent. However, in case of emergency, in order to remove the risk factors for subjects, investigators can deviate from or change the study protocol without the consent or support of the ethics committee/institutional review committee/sponsor. The deviation or change and its reasons should be submitted to the ethics committee/institutional review committee/sponsor as soon as possible, and if appropriate, the proposal modification proposal. The investigators must explain all deviations or changes in the study protocol.

